## Abstract

**Background:**

Urinary stone disease is a widespread disease with tremendous impact on those affected and on societies around the globe. Nevertheless, clinical and health care research in this area seem to lag far behind cardiovascular diseases or cancer. This may be due to the lack of an immediate deadly threat from the disease and therefore less public and professional interest. However, the patients suffer from recurring, sometimes intense pain and often must be treated in hospital. Long-term morbidity includes doubled rates of chronic kidney disease and arterial hypertension after at least one stone-related event. Observational studies, more specifically, registries and other electronic data sets have been proposed as a means of filling critical gaps in evidence. We propose a nationwide digital and fully automated registry as part of the German Ministry for Education and Research (BMBF) call for the "establishment of model registries”.

**Methods:**

RECUR builds on the technical infrastructure of Germany’s Medical Informatics Initiative. Local data integration centres (DIC) of participating medical universities will collect pseudonymized and harmonized data from respective hospital information systems. In addition to their clinical data, participants will provide patient reported outcomes using a mobile patient app. Scientific data exploration includes queries and analysis of federated data from DICs of eleven participating sites. All primary patient data will remain at the participating sites at all times. With comprehensive data from this longitudinal registry, we will be able to describe the disease burden, to determine and validate risk factors, and to evaluate treatments. Implementation and operation of the RECUR registry will be funded by the BMBF for five years. Subsequently, the registry is to be continued by the German Society of Urology without significant costs for study personnel.

**Discussion:**

The proposed registry will substantially improve the structural and procedural framework for patients with recurrent urolithiasis. This includes advanced diagnostic algorithms and treatment pathways. The registry will help us identify those patients who will most benefit from specific interventions to prevent recurrences. The RECUR study protocol and the registry’s technical architecture including full digitalization and automation of almost all registry-associated proceedings can be transferred to future registries.

**Trial registration:**

This study is registered at the German Clinical Trial Register (*Deutsches Register Klinischer Studien*), DRKS-ID DRKS00026923, date of registration January, 11^th^ 2022.

## Background

Urinary stone disease (syn. *urolithiasis*) is a widespread disease with tremendous impact on those affected and on societies around the globe. Nevertheless, clinical and health care research in this area seem to lag far behind cardiovascular diseases or cancer. This may be due to the lack of an immediate deadly threat from the disease and therefore less public and professional interest. There is a paucity of data on epidemiology and health care concerning urolithiasis in Germany and around the world. In Germany, Hesse et al. published the only available data on the incidence and prevalence of urinary stone disease in 2003 [1]. According to their data, the incidence and prevalence of urolithiasis are rising (incidence in 1979: 0.54%, 2001: 1.47%; prevalence 2001: 4.77%). This includes recurrent urolithiasis in 50% of patients within 5 years [2].

### Disease burden and socio-economic impact

The high recurrence rate of urolithiasis is in line with repeated episodes of severe pain and hospitalization. Affected patients may need multiple interventions and operations, including treatment-associated complications. Long-term morbidity includes septicemia, doubled risk of acute or permanent kidney damage, and arterial hypertension after at least one stone-related event, leading to significant limitations in quality of life [3].

In Germany, the numbers of in-hospital treatments for urolithiasis exceed those of any other urological disease including prostate cancer, bladder cancer, and benign prostatic disease [4]. Overall, urolithiasis affects approximately 10% of the population of industrial countries, which corresponds to 8 million patients in Germany [5]. Costs for work days lost and treatment are high exceeding € 500 million and 5.8 million lost working days per year in Germany in 1997 [6]. In the United States, costs of stone disease are projected to exceed $ 4.5 billion annually by 2030 [7].

### Risk factors

To date, little is known about sociodemographic and behavioral risk factors for recurrent urolithiasis [8]. Risk factors explaining recurrent stone formation in the vast majority of recurrent stone formers thus remain unaccounted for. However, evidence is pointing to specific characteristics that correlate with higher risks of recurrent stone forming: Men are more often affected than women (prevalence 5.5% vs. 4.0%) [1]. Fifty percent of patients are considered “high risk” patients with more than two stone-related events and/ or known risk factors for disease recurrence [9]. Risk factors for highly recurrent stone disease include general factors (early onset, family history of urolithiasis), specific stone compositions, diseases associated with stone formation (hyperparathyroidism, gastrointestinal disease, etc.), genetically determined diseases associated with stone formation (cystinuria, primary hyperoxaluria, etc.), and anatomical abnormalities of the urinary tract associated with stone formation [10]. Metabolic evaluations of recurrent stone formers may reveal abnormalities in urine chemistry associated with stone formation [2]. In addition, recent studies identified several gene mutations associated with nephrolithiasis [10].

### Current treatments

Available treatment modalities include medical treatment for renal colic and metaphylaxis of urolithiasis (prevention of recurrence), use of a ureteric catheter to treat hydronephrosis due to ureteral stones, and various surgical treatments to remove urinary stones (shock wave lithotripsy, ureteroscopy and percutaneous nephrolithotomy). Approximately 750.000 stone-related events are treated annually in Germany, with some patients receiving multiple treatments [11]. This includes > 130.000 surgical treatments to remove stones [12]. In the United States, costs for urolithiasis treatments exceed those for prostate cancer and benign prostatic hyperplasia [13].

### Research on urolithiasis

Overall, the level of evidence in urolithiasis-related research is low. In 2014, we reviewed the current literature on clinical urolithiasis-related trials to answer fundamental questions—e.g., “which is the best surgical treatment for patients with upper tract urinary stones?” or “how should we manage patients with recurrent urolithiasis?”.

We found levels of evidence 1 (randomized controlled trials, RCT), 2 (cohort studies), 3 (case–control studies) and 4 (case series) in 15%, 14%, 21% and 51% of trials published in 2014, respectively [14]. The reasons for low numbers of high level trials are:

Patients refrain from
being randomized, especially when established surgical treatment is involved,
e.g., shock-wave therapy vs. ureteroscopy.Explanatory trials -
e.g., RCTs performed with relatively small samples at sites with experienced
investigators and highly selected patients, may overestimate benefits and underestimate
harm. Results from these trials may not inform practice because they are
optimized to determine efficacy (performance of an intervention under ideal and
controlled circumstances) as opposed to effectiveness [15].

Observational studies and more specifically registries and other electronic data sets have been proposed as a means of filling critical gaps in evidence [16]. Clinical registries record real-world data to evaluate associations among variables on the individual (e.g. patient demographics, physical and physiologic parameters), the context (e.g. climate, working conditions) and clinical outcomes (e.g. stone recurrence). Information from registries may also be used to evaluate how patients with different characteristics respond to various treatments and to compare the performance of healthcare providers with regard to their outcomes and resource use (*effectiveness*—i.e., performance in ‘real world’ conditions) [17]. Sources of real-world data may include electronic health records and mobile applications.

### Registries in urolithiasis

In 2009 and 2010, the Clinical Research Office of the Endourological Society (CROES) implemented two clinical registries on PNL and URS treatment of urinary stones. Both registries collected data on active treatment for urolithiasis from dedicated centres around the world over a one-year period. Both registries are closed. Data from these registries are limited to the patients' perioperative course. To our knowledge, there have been no nationwide registries on urolithiasis established in Germany or any other industrialized country. However, implementation of a national registry in the U.S. was described in a recent publication [18].

### Objectives

We will implement and assess the effectiveness of the RECUR registry for recurrent urolithiasis in the upper urinary tract as a distributed multi-institutional digital registry based on the technical infrastructure of the German Medical Informatics Initiative (MI-I).

Our purpose is to answer the following research questions:

Description of disease
burden: What impact does urolithiasis have on individual patients and the
health care system?Impact of the disease on
patient-reported outcomes (PROMs, e.g. working ability, perceived restrictions
of activity and participation due to urolithiasis, stone-related quality of
life) [19, 20]: trajectories of these outcomes will be analysedSocio-economic impact
(e.g., length of hospital stay, lost working days) [6, 21]: standardized unit
costs will be applied to quantify the costs of medical resource utilization;
analyses will be carried out from the healthcare perspectiveGender-dependent impact
of urolithiasis: subgroup analyses will reveal gender-specific aspects of the
disease burden [22, 23]Determination and
validation of risk factors: How can patients at risk of stone recurrence be
identified beyond the known risk factors?Personalized medicine:
taking into account individual variability in lifestyle and nutritional habits,
sociodemographic factors (age, education, socio-economic status), genes
[24–26]: multi-level models for change will be devisedDevelopment of a risk
score to predict the probability of stone recurrenceValidation of the risk
score using longitudinal registry dataDeduction of implications
for prevention and treatmentTreatment evaluation:
Which is the optimum treatment for individual patients? [27]Risk-adjusted comparison
of outcomes for different treatment options (e.g. surveillance vs. medical
treatment vs. surgical treatment): Propensity score matching analyses will be
conducted to compare outcomes; this method will help us estimate a given treatment’s
effect while accounting for the covariates that predict receiving the
treatment.We will focus on outcomes
relevant to patients such as disease recurrence, sick leave due to
urolithiasis, perceived restrictions of activity and participation due to urolithiasis.

## Methods

### Technical infrastructure

RECUR builds on the technical infrastructure of Germany’s MI-I. The BMBF launched its medical informatics funding scheme to make data from healthcare and research more useful and meaningful [28]. The BMBF provides funding for several consortia within the scope of the MI-I. Each consortium comprises multiple university hospitals and additional partners. Key to the initiative is the establishment and interconnection of DIC by each consortium [28].

The MIRACUM Consortium (Medical Informatics for Research and Care in University Medicine) unites ten university hospitals, two universities, and a partner from the healthcare industry. Its goal is to make clinical, image and molecular/genomic data available for use in innovative research projects – both within and across multiple institutions [29]. The participating sites are the University Hospitals in Dresden, Erlangen, Frankfurt, Freiburg, Giessen, Greifswald, Magdeburg, Mainz, Mannheim, Marburg and Malteser Waldkrankenhaus in Erlangen.

The features of a clinical data warehouse (CDWH) include data integration, consolidation, and presentation [30]. Data integration is the merging of information from heterogeneous data sources, often from primary systems. In this way, the primary systems are uncoupled from further processing of the data to maintain their stability. Consolidation brings heterogeneous information together in a structured data model consisting of facts (e.g., primary and secondary diagnosis recorded for a patient) and dimensions (i.e., international statistical classification of diseases and related health problems (ICD) catalogue). In the subsequent presentation (e.g., reporting and interactive queries), such harmonized content can be used more effectively than would be possible with direct access to the individual sources. Notable examples of software platforms and data models for CDWH are i2b2, TranSMART, and OHDSI (observational medical outcomes partnership/observational health data sciences and informatics) [31]. These platforms have enabled the successful (re)use of electronic health records (EHR) in various fields, for example, disease genomics and pharmacovigilance [32].

All clinical data in RECUR will be retrieved from hospital information systems (HIS) and EHR of individual patients via DICs of the participating centres of the MIRACUM consortium. Data will remain in the local centres (decentralized or distributed registry). In addition, patients will provide patient-reported outcomes using a RECUR smartphone app. These data are also processed and stored by the DICs of the participating sites.

Analyses will be performed by submitting electronic analysis requests to the DICs according to the federated MIRACUM analysis concept.

### Target population and recruitment

The target population includes all patients with recurrent urinary stone disease (approximately 5% of the population of industrialized countries). The source population comprises all patients with recurrent urinary stone disease (≥ 2 stone-related events) evaluated and treated at participating hospitals of the MIRACUM consortium. Observational units are all patients who give their consent to participate.

Eligible patients will be offered a patient information brochure in participating centres during outpatient or inpatient visits. This brochure informs patients about the purpose of the planned registry. At the same time, the personal benefits of participation will be explained and health professionals in recruiting centres will provide detailed information if necessary. No financial incentives will be provided for participation.

If interested in participation, patients can use a downloadable app to consent and register. To increase adherence, patients can contact the study team in case of upcoming study-related questions or the technical support in case of technical problems.

### Sample size calculation

As with many registry studies investigating widespread diseases with high prevalence, sample size is not a major concern. Therefore, we did not perform sample size calculations. We aim at collecting as much and as complete data as possible by reducing a) the effort for including patients into this study and b) the size of the questionnaires to a minimum. Non-responders to the app-integrated questionnaires will automatically receive reminders to increase completeness of data. Considering the high volume of eligible patients at the participating centres, we expect an annual recruitment rate of 500 to 1000 patients.

### The RECUR patient app

Patients will be included in this study based on a signed electronic informed consent. Within this smartphone application, participants will be provided with a comprehensive patient information form. Participants are asked to sign the digital consent and to confirm that they had the opportunity to ask their treating physicians or the study team to answer any open questions concerning the registry and that they have read and understood the patient information.

After electronic consent, the RECUR app will provide participants with the digital questionnaires regarding sociodemographic data, quality of life, working ability, nutrition and physical activity. The data will be collected anonymously without identifying features such as an IP-address or user name. All data is stored securely in a public cloud infrastructure. Participants will have to present in-person to a participating centre in order to establish a pseudonymous link between their in-app responses and their EHR. Subsequently, the participating clinic can merge the patients’ existing and future responses with clinical routine data in its DIC.

Participants will receive digital questionnaires at regular intervals, e.g. monthly, to answer certain questionnaires. If patients do not complete the questionnaires, they will receive a reminder after 4 weeks. We will collect follow-ups at semiannual intervals. PROM results will also be available to both patients and their treating physicians via a local interface between patient app and hospitals using the pseudonymized link as described above. This will enable patients and their doctors to discuss the patient’s personal risk profile based on clinical findings and PROMs.

Participants may discontinue the study at any time using one of the following options: uninstalling the RECUR App, withdrawing their given consent within the app, or clicking the option to delete all personal data. It will not be possible to delete data that has already been processed.

### Data management and data safety

Clinical data for the RECUR distributed registry will be captured, processed, stored and analysed using established MI-I/ MIRACUM tools. All primary data will remain untouched in local HIS. All scientific data used for RECUR will be processed and stored in research data repositories after transfer into each DIC. No central repository will be established. We will use the established MI-I tools for standardization of data, their quality assurance and protection. The data protection policy of RECUR includes the following: (1) pseudonymization of data stored in research data repositories, (2) data security and protection measures on the level of the computational centre of the participating centres, (3) distributed privacy-preserving analysis tools (no transfer of individual patient data between sites or a central server).

Key performance indicators (number of participating patients, frequency of patients providing PROMs, achievement of milestones) and data quality measures (completeness, correctness, data accuracy) of the registry will be checked regularly at each site. A performance and quality report will be generated centrally at the Medical Centre—University of Freiburg at regular intervals.

### Data set

The full data set will be composed out of three sets of characteristics. This includes the participants’ clinical data (diagnoses, treatments, laboratory data, radiology findings, medication) available via the data integration centres (catalogue of characteristics [COC] I). COC II contains all patient reported outcome measures (PROMs) as provided by the participants via the RECUR smartphone application. A third COC will contain all information retrieved by yearly follow-ups of the clinical DIC data and PROMs via the patient app.

### Outcomes

Primary outcome variables of the registry are “stone recurrence” and “stone-related quality of life” using the German version of the Wisconsin Stone Quality of Life Questionnaire (WISQOL) [33]. Secondary outcomes include pain, functional restrictions, working ability, sick leave, and sequelae. Determining and confounding variables include individual and external risk factors.

Individual risk factors include clinical findings (size, weight, co-morbidity), laboratory results (including stone composition), radiology reports (including number, size and location of stones), medication, etc. (captured via DICs) and sociodemographic and lifestyle variables (nutrition, physical activity). Patients will be divided into risk groups to determine the effectiveness of different treatments. External risk factors include all interventions such as secondary prevention measures, non-surgical and surgical treatments for urolithiasis.

### Data analysis

To answer research question 1 (description of disease burden), descriptive analysis methods will be used. The WISQOL will be analysed following the specifications of the developers [33]. No monitoring of PROMs during the study will take place. We will carry out an analysis of patterns of missing items and will take appropriate measures to deal with them.

Regarding research question 2 (determination and validation of risk factors), we expect missing data, that might occur not completely at random. Therefore, multiple imputations will be applied to reduce the chance of bias from missing data. Two-level multiple logistic regression models with the dependent variable stone recurrence will be conducted to account for cluster effects (patients are nested within centres). By using Receiver Operating Characteristics (ROC) analyses, we will determine the predictive power of the risk factors. The Youden Index and area under the curve (c statistic) will be calculated. As ROC curves do not consider time to event and right censoring, we will complement this analysis via survival analysis techniques like Kaplan–Meier or Cox regression analyses.

Since prognostic models derived from multivariable regression analysis lead to overestimated predictions when applied in new patients, we will internally validate our model with bootstrapping techniques. For external validation, it is essential to evaluate the performance of the model in a sample independent from those used to develop the model. This will be realized by comparing the prognostic capacity in the data set acquired in the first year with that in the second year.

For treatment evaluation (research question 3), propensity score matching will be applied. This method is increasingly used as an alternative to traditional regression to balance differences between treatment groups in descriptive and causal comparisons. To account for the nested data structure, propensity-score-weighted estimators for clustered data will be applied. Analyses corresponding to research question 1 will be conducted every six months, the other analyses annually.

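### The recurrence risk analysis rests on logistic regression with no time window, so its predicted probability depends on the mix of follow-up times at the data cut

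*Protocol article*

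**What the plan says.** The Objectives section of the protocol article plans a score that gives the probability of stone recurrence, and its later validation on registry data. The Outcomes section makes recurrence one of two primary outcomes: "Primary outcome variables of the registry are “stone recurrence” and “stone-related quality of life". Neither section attaches a time window to it.

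The Data analysis section sets out the method for risk factors: "Two-level multiple logistic regression models with the dependent variable stone recurrence will be conducted to account for cluster effects". ROC analysis follows, and "The Youden Index and area under the curve (c statistic) will be calculated". The section concedes a weakness of this step, "As ROC curves do not consider time to event and right censoring", and names as its remedy that "we will complement this analysis via survival analysis techniques like Kaplan–Meier or Cox regression analyses". Internal validation is by bootstrap. External validation compares prognostic performance in first-year data with that in second-year data. Risk-factor analyses are repeated every year.

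On accrual, the Sample size calculation section says "we expect an annual recruitment rate of 500 to 1000 patients". The Abstract (Methods) says "Implementation and operation of the RECUR registry will be funded by the BMBF for five years", with the registry meant to continue afterwards. The Machine learning section announces a statistical analysis plan, which is not shown.

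**The concern.** With continuous entry and annual data cuts, patients in any one analysis have been observed for different lengths of time. A plain logistic model with recurrence as a yes/no outcome codes a patient who has been recurrence-free for three months in the same way as one who has been recurrence-free for years. The article recognises this weakness in the ROC curve, but the logistic model that feeds the curve shares it, and survival analysis is given only a supporting role.

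Three things are at stake:

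- **The predicted probability.** It changes from one annual analysis to the next with no change in underlying risk, and a clinician could not say what period it refers to.
- **The validation.** If first-year and second-year data mean enrolment cohorts, the two differ in follow-up as well as in patients.
- **Some odds ratios.** A factor that becomes more or less common during recruitment is associated with length of follow-up, and so with recorded recurrence, even if it has no effect.

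**Working it through.** The article gives no event count, power or predicted risk for this analysis, so there is no figure to reproduce. The calculation below only shows the size of the effect.

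**Inputs**

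- Recurrence of 50% within 5 years: Background section, used as an illustrative rate.
- Continuous recruitment and annual analyses: Sample size calculation and Data analysis sections.
- Five years as the longest period considered: the funding period in the Abstract. The article states no follow-up range.
- Assumed: constant hazard, uniform entry, no dropout.

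**Step 1: hazard and true risks.** λ = −ln(0.5)/5 = 0.1386 per year. Risk by time t is 1 − exp(−λt), which gives 12.9% at 1 year, 24.2% at 2, 34.0% at 3 and 50.0% at 5.

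**Step 2: pooled proportion at a data cut.** For follow-up spread evenly from a to b years, the proportion with a recorded recurrence is 1 − [exp(−λa) − exp(−λb)] / [λ(b − a)].

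| Cut at end of year | Pooled proportion |
|---|---|
| 1 | 6.6% |
| 2 | 12.7% |
| 3 | 18.2% |
| 4 | 23.2% |
| 5 | 27.9% |

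For year 5: 1 − (1 − 0.5)/0.693 = 0.279. This equals the true risk at t = −ln(1 − 0.279)/0.1386, about 2.4 years, a horizon that nobody chose.

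**Step 3: by enrolment year at the year-5 cut.** The same formula with one-year bands gives 46.4%, 38.4%, 29.2%, 18.7% and 6.6% for enrolment years 1 to 5. The odds ratio for year 1 against year 5 is (0.464/0.536)/(0.066/0.934), about 12.2 from unrounded values, with identical underlying risk.

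**Step 4: the validation comparison.** At the end of year 2, the first-year enrolment cohort (1 to 2 years observed) shows 18.7% and the second-year cohort (0 to 1 year) 6.6%, an odds ratio of 3.2. This applies only if the two data sets are enrolment cohorts.

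**Step 5: a factor with no effect.** Let its prevalence rise over enrolment years as 20, 25, 30, 35, 40%. With the risks of step 3:

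- exposed: (0.20×0.464 + 0.25×0.384 + 0.30×0.292 + 0.35×0.187 + 0.40×0.066)/1.5 = 0.246
- unexposed: (0.80×0.464 + 0.75×0.384 + 0.70×0.292 + 0.65×0.187 + 0.60×0.066)/3.5 = 0.293
- odds ratio: (0.246/0.754)/(0.293/0.707) = 0.79

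The same 5-point yearly rise gives 0.92 at a 2-year cut and 0.87 at a 3-year cut. A rise from 10% to 50% gives 0.61 at 5 years. With constant prevalence the odds ratio is 1.00. In simulation with drifting prevalence (40% to 60%, and 20% to 80%), the person-time rate ratio for a null factor stayed at 1.00 to 1.01.

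**Step 6: a real factor unrelated to enrolment date.** With hazard ratio 2, prevalence 50% and 50% overall risk at 5 years, the odds ratio is 2.15 under mixed follow-up and 2.62 at a fixed 5 years. Predicted risks are 36% and 21%, against 62% and 38%.

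**The case against.** The strongest reply is that the authors have seen the problem. They name right censoring and plan Kaplan–Meier or Cox analyses, and the horizon and minimum follow-up could be set in the analysis plan that is not shown. Yearly collection of clinical follow-up (Data set section) would be compatible with a fixed-interval binary outcome, for which logistic regression is acceptable. The article also does not say outright which model produces the score.

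Much of this is fair. A reader might infer that censoring was overlooked; it was not. What stands is that the Data analysis section ties the ROC curve, Youden Index and c statistic to the logistic model and gives survival analysis only a complementary role. An analysis plan that based the score on survival would have to reverse those roles. Multiple imputation is planned for missing data, but the article does not present it as a treatment of administrative censoring.

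Three stronger readings are tempting and are not supported:

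- **That predicted risks would be too low at every horizon.** The illustrative 27.9% exceeds the 1-year and 2-year risks (12.9% and 24.2%). Only horizons beyond about 2.4 years are understated.
- **That odds ratios in general absorb enrolment date.** This needs a factor that drifts during recruitment. The article gives no such drift, and the centre level in the planned model would take up at least part of the effect of a late-joining centre.
- **That follow-up is stated to run from zero to five years.** The range is inferred from continuous accrual and the funding period; early cuts span less.

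The absence of calibration measures is not a fault in itself, since a condensed article may leave these to the analysis plan.

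**Conclusion.** The point holds in a limited form. As written, the main recurrence analysis yields a probability that reflects the follow-up mix at the data cut and has no defined horizon. In the illustration it rises from 6.6% to 27.9% between the year-1 and year-5 cuts while the underlying hazard stays the same. Confounding by enrolment date is conditional: about 0.79 at a 5-year cut for a null factor rising from 20% to 40%, less at earlier cuts, and none without drift.

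The figures rest on the assumed constant hazard, uniform entry and no dropout. The 50% rate is a background figure for stone patients, whereas the registry enrols patients with at least two stone-related events, and the Discussion expects some loss of participants. The numbers therefore show scale and correct nothing in the article. The change is worth making before the first annual risk-factor analysis, because it concerns a primary outcome and a named objective. It does not put the registry itself in doubt.

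**What to change.** In the Data analysis section, reverse the roles of the two approaches:

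- Make a time-to-event model, with centre as a random effect or stratum, the basis of the risk score, any cut-off, the bootstrap and the year-1/year-2 validation. A binary outcome at a fixed horizon would also serve if censoring is handled, for example by inverse-probability-of-censoring weights.
- State the horizon or horizons to which the predicted probability refers, each within the follow-up available at the data cut.
- Report discrimination and calibration at the stated horizon.
- Keep the plain logistic/ROC analysis as a sensitivity analysis.

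Survival methods are already planned, so no new type of analysis is introduced. The cost is more than wording, however. The survival model has to be fitted within the federated system, where individual patient data do not leave the sites, and the analysis relies on recurrence dates from the routine clinical data. The article does not say how complete those dates will be.
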